### Handling of missing data

Participants with missing data on post-intervention outcome assessment (retrospective questionnaire) will be excluded from analysis.

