
There are several lines of evidence to suggest that N-acetylcysteine (NAC) could be of potential benefit for compulsive eating. NAC, a cysteine prodrug, has been shown to reduce several compulsive behaviours, such as use of addictive drugs and compulsive hair pulling and skin picking [16]. Abnormal regulation of glutamate in the striatum has been implicated in the pathophysiology underlying compulsive behaviors [17, 18]. Therefore, the mechanism of action of NAC may involve modulation of the cysteine-glutamate antiporter, known as system xc-, and the glial glutamate transporter, GLT-1, which play a key role in glutamate homeostasis and influence glutamate transmission [19]. Repeated use of drugs of abuse such as cocaine leads to persistent reduction of cysteine-glutamate exchange via system xc- in brain areas involved in hedonic motivated behaviour such as the nucleus accumbens [20–23] which disrupts the level of extracellular glutamate. Similarly, drugs of abuse also reduce the expression of GLT-1 in the nucleus accumbens [20, 21]. Administration of NAC restores xc-function and ameliorates drug-seeking behavior [23–25]. Likewise, NAC administration upregulates GLT-1 expression [21, 26] which mediates NAC inhibition of cue-induced reinstatement of cocaine seeking [26]. Restoring extracellular glutamate with NAC has been shown to inhibit excitatory synaptic activity in the nucleus accumbens via activation of group II metabotropic glutamate receptors (mGluR2/3) [27]. In humans, NAC treatment at 2400 mg/day for 4 weeks reduces tobacco use (32 participants in total) [20] and cocaine use (23 participants in total) [28]. Our laboratory has shown that NAC reduces compulsive eating behaviour in diet-induced obese rats [29]. NAC has also been shown to reduce binge-like eating in a model where rats were given daily limited access (30 min) to a highly palatable diet [30] and reduce food-seeking behavior in a rat model of cue-induced reinstatement [31]. As yet, there are no studies examining the effect of NAC on compulsive eating in humans. One small study has examined the effects of NAC on eating behavior in people with bulimia nervosa [32]. This open-label study examined the effect of NAC on binge-purge frequency in eight participants, of whom only two completed the 12-week intervention (the following reasons for attrition were reported: loss to follow up, lack of efficacy, or experiencing side effects [32], thus limiting the conclusions that can be drawn. Therefore, more research is required to evaluate the efficacy of NAC for compulsive eating.

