### Aims

The primary aim of this study is to assess the feasibility of delivering a 12-week NAC intervention in people with loss of control eating. The secondary objective is to estimate the clinical efficacy of NAC to inform a sample size calculation for future research. In addition, we aim to explore the performance of self-reported measures of eating behaviors and mood using EMA compared with retrospective questionnaires.

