### Outcome measures

The primary outcomes are participant retention rate, recruitment rate, and medication adherence. Retention rate will be calculated as the proportion of individuals who completed retrospective questionnaires at week 12. Recruitment rate will be assessed by calculating the number of recruited participants per month. Adherence to medication will be the percentage of doses taken, based on capsule count. The secondary outcome is change in Eating Loss of Control Scale score from baseline to week 12. The exploratory outcomes include the following:Adherence with EMA protocol (percentage of EMA surveys completed; percentage of participants who completed at least 80% of EMA surveys);Concordance between EMA and retrospective measures (internal consistency, convergent validity, and sensitivity to detect treatment outcome);Change of scores in the drivers of eating and eating behaviour from baseline to week 12:Emotional eating (Palatable Eating Motives Scale: Coping subscale and Emotional Eating Scale);Food craving (Food Craving Inventory);Preoccupation with food (Reward-based Eating Scale);Perceived stress (Perceived Stress Scale).

The outcomes will be assessed using both retrospective questionnaires (described below) and EMA.

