#### Questionnaires

Sixvalidated questionnaires, including the Eating Loss of Control Scale [33], Palatable Eating Motives Scale: Coping Subscale [40], Food Craving Inventory [41], Reward-Based Eating Scale [42], Perceived Stress Scale [43], and Emotional Eating Scale [44], will be administered during baseline and post-NAC treatment assessment. Participants will be asked to complete these questionnaires electronically.

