### Statistical analysis

All participants who received at least the first dose of study drug and provided at least 1 post baseline assessment will be included in the analysis. Data will be cleaned and checked for accuracy. Demographic characteristics will be summarized as proportions for categorical data and means and standard deviations for continuous data or medians as appropriate. For primary outcomes, retention rate will be calculated as the proportion of individuals who completed retrospective questionnaires at week 12; recruitment rate will be calculated as the total number of participants recruited divided by the total number of months that the trial recruited for. Secondary and exploratory outcomes will be reported as estimates of effects (95% confidence interval). Pearson or Spearman correlation will be used to analyze the concordance between EMA and retrospective measures (convergent validity), and reliability (internal consistency) will be examined with Cronbach’s alpha. Compliance rate will be estimated from the average number of EMA surveys completed out of all administered surveys.

Adverse events will be reported as the number and percentage of participants reporting adverse events. Other information about each adverse event including start date, stop date, severity, relationship, expectedness, outcome, and duration, including adverse events leading to premature discontinuation from the trial intervention and serious treatment-emergent adverse events, will also be collected.

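### The Eating Loss of Control Scale change is estimated only in week-12 questionnaire completers, so as a planning figure for a future trial it is likely, though not certain, to overstate the change among all treated participants

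*Protocol article*

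**What the plan says.** Under Handling of missing data, the protocol article gives one rule: "Participants with missing data on post-intervention outcome assessment (retrospective questionnaire) will be excluded from analysis".

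The Statistical analysis section describes a different and wider set of people to be analysed. It opens: "All participants who received at least the first dose of study drug and provided at least 1 post baseline assessment will be included in the" … The two are not reconciled.

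The outcome at stake is defined under Outcome measures: "The secondary outcome is change in Eating Loss of Control Scale score from baseline to week 12". Table 1 and the Questionnaires section place the retrospective questionnaires at baseline and after treatment only, with no score in between. On delivery, the article says: "Participants will be asked to complete these questionnaires electronically".

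The use of the estimate is set out under Aims: "The secondary objective is to estimate the clinical efficacy of NAC to inform a sample size calculation for future research".

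The Background describes an earlier open-label NAC study in bulimia nervosa, "in eight participants, of whom only two completed the 12-week intervention", and adds that "the following reasons for attrition were reported: loss to follow up, lack of efficacy, or experiencing side effects".

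**The concern.** Retention is defined as completing the week-12 questionnaires. The people removed by the missing-data rule are therefore exactly those counted as not retained, and the efficacy estimate describes only those who stayed to answer.

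That would do no harm if non-completers changed as much as completers. The protocol's own account of earlier attrition gives reason to doubt it, because a person who leaves for lack of efficacy is missing for a reason tied to the outcome. In a single-arm before-and-after design there is no comparator group undergoing similar selection, so any selection passes straight into the estimate.

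The consequence lies in the next trial. If its planners take the completer change as the effect to be expected in everyone treated, that trial may be too small. The Discussion's limitations acknowledge that uncontrolled designs can give larger effects, but they do not mention attrition, which is a separate source of inflation.

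**Working it through.** **1. The plan's own figure.** The Sample size estimation section gives 36 participants for retention of 80% against 60%, with 80% power at p < 0.05 by the exact binomial test. Read as one-sided, this reproduces. With n = 36 the rule is at least 27 retained, with a type I error of 0.0449 and power of 0.832. No smaller n reaches 80% (n = 33 just misses, at 0.79996). The retention figures can therefore be taken as the plan's working assumptions.

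**2. How many are excluded.** At 80% retention, 36 × 0.8 = 28.8, so about 29 are analysed and about 7 are excluded.

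**3. Effect on the mean.** Let r be retention, m_c the mean change in completers, m_d the mean change in non-completers, and k = m_d / m_c.

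- All-treated mean = r·m_c + (1 − r)·m_d = m_c·[r + (1 − r)k]
- Overstatement = m_c / all-treated mean = 1 / [r + (1 − r)k]

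The documents give no value for k, so it is an assumption and is shown as a range at r = 0.8:

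| k | r + (1 − r)k | Overstatement |
|---|---|---|
| 0 (no change on average) | 0.80 | 1.25 |
| 0.5 (half the change) | 0.90 | 1.11 |
| 1 (same change) | 1.00 | 1.00 |
| 1.25 (a quarter better) | 1.05 | 0.95 |

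**4. Effect on a future sample size, with k = 0 and r = 0.8.** Required n is proportional to (SD / mean)², so the answer depends on the SD as well as the mean.

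- *SD unchanged* (non-completers average zero with a similar spread): factor = 1 / 0.8² = 1.56.
- *Non-completers have exactly zero change*: the SD shrinks too. With completer SD s and mean m, variance = r·s² + r(1 − r)·m². Taking m/s = 0.5 as an assumption and s = 1, variance = 0.8 + 0.16 × 0.25 = 0.84 and mean = 0.8 × 0.5 = 0.4. Factor = 0.5² × 0.84 / 0.4² = 1.31.

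As an illustration, take a two-arm trial planned on a standardised effect of 0.5 (assumed; two-sided 0.05, 80% power), which needs 63 per arm. With the SD unchanged the effect becomes 0.4 and the need is 99 per arm. With the factor of 1.31 it is about 63 × 1.31 ≈ 83 per arm.

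**5. The two analysis rules side by side.** Someone who took a dose and gave only, say, a week-6 safety assessment or capsule count is in the Statistical analysis set but is excluded by the missing-data rule. If the missing-data rule were applied to the retention outcome, only completers would remain in the denominator and retention would be 100% by construction. The Sample size section speaks of enrolled participants, so this is presumably not intended. Neither the missing-data section nor the analysis section says so.

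**The case against.** The strongest reply is that the bias is not demonstrated. The only evidence is eight people with bulimia nervosa, whereas this trial enrols adults with as little as one loss-of-control episode in the past month. Loss to follow-up is also listed among the reasons and no split is given, so the number who left for lack of efficacy is unknown. This stands. It limits the claim to a likely direction, and the table shows that the sign reverses if non-completers did better.

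A reader might go further and infer that the plan tolerates 40% missing data, and that a future trial could then be undersized by 1 / 0.6² = 2.8 times. The documents do not support that. The 60% rate is the plan's worst case and its stop criterion, so it describes a pilot that would not lead on to a trial, and the factor also holds the SD fixed.

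A reader might also infer that people who stop NAC are lost to the analysis. The protocol does not say so. Retention is defined by answering the questionnaire rather than by continuing treatment, so someone who stops NAC but answers at week 12 is analysed.

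It is fair to add that the Discussion says efficacy is not the focus, and that sensitivity analyses are often left to a statistical analysis plan that is not shown here. The point does not rest on a missing sensitivity analysis. It rests on a rule the article does state, applied to an estimate to which the article gives a definite use.

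**Conclusion.** The point holds in a limited form. As written, the secondary estimate is a completers-only estimate intended for sample size planning, and the protocol itself reports some outcome-related attrition in earlier work. Overstatement is the expected direction but is not established.

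At the planned 80% retention the overstatement is 1.25 times if non-completers average no change, 1.11 times if they improve half as much, and absent if they match completers. In the no-change case a future trial would need roughly 1.3 to 1.6 times as many participants. The lower end assumes exactly zero change in non-completers and a completer mean/SD of 0.5; the upper end assumes an unchanged SD. Both carry the pilot's before-and-after change into the next trial as its effect size. That step has its own weakness, which the Discussion already concedes in part, so these factors do not show that a future trial would in fact be underpowered.

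The mismatch between the missing-data rule and the stated analysis set needs no assumption: it is there in the text.

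**What to change.** 1. State that the electronic week-12 questionnaires are sought from every enrolled participant, whether or not they are still taking NAC. This reduces missing data at source and makes explicit something the article leaves open.
2. Label the main result as completers only. Add a sensitivity analysis in all dosed participants with a baseline score, assigning no change to those with a missing week-12 score and then a range of other values. Carry the conservative value into sample size planning and state which SD goes with it, since filling in zeros shrinks the SD as well as the mean.
3. Reconcile the Handling of missing data rule with the analysis set in Statistical analysis. State that the exclusion does not apply to retention, whose denominator is all enrolled participants.

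A repeated-measures model is not a substitute. With only two time points a non-completer contributes nothing but a baseline score, and such a model does not deal with drop-out driven by an unobserved lack of response.

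The cost is a few lines of wording, a survey link to anyone who has stopped treatment, and one short extra analysis. The downside is that the headline change may be smaller.

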### Statistical analysis

All participants who received at least the first dose of study drug and provided at least 1 post baseline assessment will be included in the analysis. Data will be cleaned and checked for accuracy. Demographic characteristics will be summarized as proportions for categorical data and means and standard deviations for continuous data or medians as appropriate. For primary outcomes, retention rate will be calculated as the proportion of individuals who completed retrospective questionnaires at week 12; recruitment rate will be calculated as the total number of participants recruited divided by the total number of months that the trial recruited for. Secondary and exploratory outcomes will be reported as estimates of effects (95% confidence interval). Pearson or Spearman correlation will be used to analyze the concordance between EMA and retrospective measures (convergent validity), and reliability (internal consistency) will be examined with Cronbach’s alpha. Compliance rate will be estimated from the average number of EMA surveys completed out of all administered surveys.

Adverse events will be reported as the number and percentage of participants reporting adverse events. Other information about each adverse event including start date, stop date, severity, relationship, expectedness, outcome, and duration, including adverse events leading to premature discontinuation from the trial intervention and serious treatment-emergent adverse events, will also be collected.

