### Sample size estimation

Sample size calculation was based on progression criterion for a pilot study as recommended by Consolidated Standards of Reporting Trials CONSORT [38]. Retention rate, defined as the percentage of individuals who complete the retrospective questionnaires at week 12, was used for sample size calculation. A total sample of 36 participants are required assuming at least 80% of enrolled participants are retained in the study compared to a worst-case retention rate of 60% or less in a one sample *t*-test with 80% power at *p* <0.05 based on the exact binomial test. The cut-off points of 60% and 80% set as the “stop” and “go” criteria provides sufficient sample size and power for the assessment of the primary feasibility outcome with the lowest expected denominator (e.g., retention rate).

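### Two exclusion rules, limited to no outcome, conflict with the enrolled-participant basis of the retention criterion; one of them, applied as written, makes retention 100%

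*Protocol article*

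**What the plan says.** Four places in the protocol article bear on who is counted.

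- **Sample size estimation** sizes the trial "assuming at least 80% of enrolled participants are retained in the study compared to a worst-case retention rate of 60% or less". It sets 60% and 80% as the stop and go criteria and defines retention by completion of the retrospective questionnaires at week 12.
- **Outcome measures** makes retention a primary outcome: "Retention rate will be calculated as the proportion of individuals who completed retrospective questionnaires at week 12". The denominator is only the word individuals. Adherence, also primary, is the percentage of doses taken by capsule count, with no population named.
- **Handling of missing data** reads, in full: "Participants with missing data on post-intervention outcome assessment (retrospective questionnaire) will be excluded from analysis".
- **Statistical analysis** opens with one inclusion rule, covering those "who received at least the first dose of study drug and provided at least 1 post baseline assessment will be included in the analysis". The same paragraph then defines the primary outcomes, again with "retention rate will be calculated as the proportion of individuals who completed retrospective questionnaires at week 12", and gives no other analysis set for them.

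**The concern.** A retention rate needs the people who left in its denominator. The missing-data rule removes exactly those people, because lacking the week-12 questionnaire is what not being retained means. The Statistical analysis rule removes a subset of them: those who left before giving any post-baseline data. Neither sentence says that it applies only to the secondary and exploratory change scores.

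The two rules also differ from each other. A participant seen in person at week 6 (Safety monitoring) who never completes the week-12 questionnaire is included under one and excluded under the other.

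Retention is the outcome that sized the trial and the one that carries the stop and go thresholds. If the denominator shrinks with drop-out, a trial that should stop or be reconsidered can be reported as having met the go threshold. Early loss is a realistic prospect: the Background describes an earlier 12-week open-label NAC study in which two of eight participants completed, with loss to follow-up among the reasons.

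**Working it through.** **Inputs.** From Sample size estimation: n = 36, null retention 0.60, target retention 0.80, 80% power, p < 0.05, exact binomial test. Assumed: *e*, the share of drop-outs with no post-baseline assessment. The document gives no value, so a range is shown.

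**1. The plan's own figure.** With X ~ Bin(36, p) and a one-sided 5% level (sidedness is not stated):

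- P(X ≥ 27 | p = 0.60) = 0.0449, so the test rejects at 27/36 or more.
- P(X ≥ 27 | p = 0.80) = 0.832.

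So 36 is reproduced as a one-sided exact design. Read as two-sided (upper tail 0.025), the test needs 28/36 and has power 0.716, so the one-sided reading is the one that fits. The calculation takes all 36 enrolled as the denominator. On that basis the 80% go threshold needs 29 completers (29/36 = 80.6%; 28/36 = 77.8%), and P(X ≥ 29 | p = 0.60) = 0.0075.

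**2. The missing-data rule applied to retention.** Numerator and denominator are both the week-12 completers, so retention = c/c = 100% for any c.

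**3. The Statistical analysis rule alone.** Completers c ~ Bin(36, r). Each non-completer stays in the denominator with probability 1 − *e*. The expected apparent retention is r / (1 − (1 − r)*e*); with r = 0.60 this is 0.60 / (1 − 0.40*e*). The last two columns are exact sums over c and over the number of non-completers kept. The test in the last column uses the one-sided 5% critical value for whatever denominator results.

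| *e* (assumed) | Expected apparent retention | P(observed ≥ 80%) | Type I error of the exact test |
|---|---|---|---|
| 0 (all 36 enrolled) | 60.0% | 0.75% | 4.5% |
| 0.10 | 62.5% | 1.7% | 6.4% |
| 0.25 | 66.7% | 5.3% | 14.6% |
| 0.50 | 75.0% | 29.3% | 43.9% |
| 0.75 | 85.7% | 81.2% | 85.7% |

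**4. One data set, three answers.** Suppose 26 of 36 complete week 12 and four of the ten drop-outs have no post-baseline assessment.

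- All enrolled: 26/36 = 72.2%, below go; P(X ≥ 26 | 36, 0.60) = 0.090, test not met.
- Statistical analysis rule: 26/32 = 81.2%, above go; P(X ≥ 26 | 32, 0.60) = 0.009, test met.
- Missing-data rule: 26/26 = 100%.

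**5. Adherence, as illustration only.** If completers take 90% of doses and drop-outs 20% to 30% (assumed rates), then at 60% retention adherence over all enrolled is 0.6 × 90 + 0.4 × 20 = 62% to 0.6 × 90 + 0.4 × 30 = 66%. Completers alone would show 90%. This is the extreme set by the missing-data rule. Under the Statistical analysis rule, drop-outs with a week-6 capsule count would remain and the gap would be smaller.

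**The case against.** The best defence is that the enrolled denominator is already there. Sample size estimation speaks of enrolled participants, and 36 reproduces on that basis. For retention, a missing questionnaire is an observed failure and not a missing value, so a missing-data rule need not be read as governing it; to read it so would make the stop and go criteria meaningless. The Statistical analysis paragraph also computes recruitment rate over everyone recruited, so its opening rule cannot cover every outcome. The two rules might be two levels: early data count for adverse events and the week-6 capsule count, while change scores need the questionnaire. And because Safety monitoring schedules a week-3 online survey, *e* may be small.

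Much of this stands as a guide to what was probably intended. It does not change what is written: neither rule carries a limit, the retention sentence names no denominator, and the reader must infer the exception.

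Some stronger readings are tempting but not supported:

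- *The primary outcomes are inflated.* They can be. The sample-size text points the other way, so the document contradicts itself without settling on a denominator free of drop-outs. Recruitment rate is not affected at all.
- *The Statistical analysis rule gives 100%.* It does not, because drop-outs with any early assessment stay in. Only the missing-data rule gives that result.
- *EMA compliance is inflated too.* It is exploratory and has its own stated denominator, the surveys administered. Counting scheduled surveys instead would be a choice of estimand.
- *The plan must count unreturned capsules as not taken.* That too is a choice of estimand, and such rules are commonly left to a fuller document.

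**Conclusion.** Wrong as written. The exclusion rules, followed literally, contradict the enrolled basis on which the trial was sized and its stop and go thresholds set. Under the missing-data rule retention is 100% whatever happens; this follows from the definitions and needs no assumption. Under the Statistical analysis rule the bias runs from slight to decisive. At true retention of 60% the chance of appearing to reach 80% goes from 0.75% to between 1.7% and 81% as *e* goes from 10% to 75%. That range rests on the assumed *e* and on drop-outs behaving independently. The upward bias in adherence is likely in direction if the analysis is limited to those who stayed, but the document offers no basis for its size. That the enrolled denominator was meant is plausible; the text needs to say so before a stop/go decision rests on it.

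**What to change.** Make three changes of wording.

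1. In Outcome measures and Statistical analysis, define retention as the number completing the week-12 retrospective questionnaires divided by all enrolled participants (planned 36), in line with Sample size estimation.
2. State that capsule-count adherence is reported over all participants who started, or were dispensed, NAC, and not only over completers.
3. Limit the exclusions in Handling of missing data and Statistical analysis to the secondary and exploratory change-score analyses. Reconcile the two, so that it is clear whether someone with early post-baseline data but no week-12 questionnaire is in or out of each analysis.

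The cost is wording only: no extra data, visits or participants. The reported feasibility percentages may be less favourable than under the present text.
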